##### Potential adverse effects management

2.7.2.2

Ayahuasca has been demonstrated to be safe in naturalistic (35, 108) and clinical settings, across varying dosages and multiple administrations (26, 109–112). To enhance participant safety, individuals with a history of psychosis, medical complications, hypertension, or potential pharmacological interactions are excluded. While physically safe, the acute effects of ayahuasca are often challenging and not necessarily pleasant.

###### Acute effects

2.7.2.2.1

Nausea and vomiting are common during ayahuasca sessions (32), so each participant will have a bucket, tissue, and water placed next to their mat to facilitate vomiting without needing to leave for the restroom. If a participant experiences significant distress, agitation, anxiety, fear, or paranoia, facilitators will provide reassurance and encourage acceptance and curiosity toward the challenging internal experiences. Grounding techniques, including deep breathing, mindful awareness (learned before the session), and progressive muscle relaxation, may also be suggested. Participants feeling overwhelmed by the group experience may be temporarily moved to a quiet space and remain under a direct facilitator’s supervision.

###### Post-acute effects

2.7.2.2.2

The effects of ayahuasca are expected to last 5-6 hours, although participants may rest on their mats for up to 4 additional hours while listening to calming music under professional supervision. In cases of anxiety or distress, grounding techniques and emotional regulation strategies will be employed. If nausea or vomiting persists, antiemetic teas, such as ginger or chamomile, will be offered. Vital signs, including blood pressure, will be closely monitored in participants exhibiting adverse effects after the ayahuasca session.

###### Rescue medication

2.7.2.2.3

After monitoring post-acute effects for 4 hours, the medical team will evaluate the need for rescue medication if clinically indicated. In cases of severe anxiety, 1 mg of lorazepam may be offered, and in cases of agitation or psychosis, 5 mg of olanzapine may be administered, with the option to repeat the dose after an hour if symptoms persist. In extreme cases of severe agitation, where there is a risk of self-harm or the participant hurting other people, intramuscular administration of 0.5 mg of clonazepam may be required. For cases of severe and persistent hypertension (SBP > 180 mm Hg, DBP > 120 mm Hg), participants will be closely monitored and lorazepam 1mg may be administered. If the hypertension persists after 30 minutes, 25 mg of captopril may be administered, with a second dose after 30 minutes if necessary. If systolic/diastolic blood pressure persists above 180/120mmHg, 10mg of amlodipine may be administered, with a subsequent referral to an emergency service to assess for target organ damage. Metoclopramide (10 mg) may be offered for severe, persistent nausea and paracetamol (500 mg) if the participant experiences severe headaches. Participants will remain under medical supervision for at least 12 hours after the ayahuasca experience: any residual symptoms will be addressed during subsequent psychotherapy sessions.

The excitement component of the Positive and Negative Syndrome Scale (PANSS-EC) (113) will be evaluated by the physician 24 hours after ingestion for all participants.

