### Psychedelic-assisted grief therapy

1.1

Psychedelic-assisted psychotherapy (PAP), a therapeutic approach augmenting talking therapy with psychedelic substances, has been recently classified as a potential breakthrough treatment for psychiatric illness (19). PAP is demonstrating promising outcomes in treating a wide range of mental health issues, ranging from depression to post-traumatic stress disorder, suggesting this efficacy may be transdiagnostic (20, 21). Controlled studies to date have been primarily focused on MDMA-assisted therapy for PTSD (22) and psilocybin-assisted therapy for treatment-resistant depression (23), but it has been proposed that psychedelics could also serve as a prophylactic or preventive intervention with the potential to improve quality of life, well-being, creativity, and personal and spiritual growth (24, 25).

Ayahuasca, a traditional indigenous medicine, has been investigated as a potential treatment for treatment-resistant depression (26). Several studies have evidenced that individuals who regularly use ayahuasca in a communal setting exhibit a higher level of general well-being, increased physical activity, and balanced diet than the general population (27–29). While ayahuasca may not cause physical or psychological dependence, and serious adverse effects are uncommon in healthy individuals (30), some users have reported experiencing psychological distress during its acute effects (31). In a global survey involving 10,836 participants, 2.3% reported requiring medical support following ayahuasca use (32). Additionally, there have been a few documented instances where its consumption has been associated with the emergence of psychotic episodes (33). Nevertheless, most adverse effects can be mitigated by conducting a thorough assessment of participants’ health status prior to administration, ensuring the composition and purity of the ayahuasca preparation, administering an appropriate dosage, and avoiding potential drug interactions (30) (see Section Potential Adverse Effects Management).

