### Procedure

2.3

Participants will be recruited through the newsletter, webpage, and social media accounts of the Beckley Foundation, Beckley Med, MIND Foundation and the International Center for Ethnobotanical Education, Research and Service (ICEERS), all of them European institutions dedicated to psychedelic research and education. Upon receiving the request to participate in the trial, the participant will be prompted to complete a short online questionnaire to screen for inclusion criteria. Those who meet the inclusion criteria will attend a video-call interview with the principal investigator (DG) to learn more about what their participation would entail and to screen whether any exclusion criteria are met. They will also be informed about the need to verify their blood pressure range with a general practitioner to prevent potential ineligibility, given that blood pressure measurement is taken on-site before each ayahuasca session. Then, those who are eligible will provide informed consent. Assessments will be conducted online at baseline (T0), during treatment (T1 and T2), at post-intervention (T3), and at 3-month follow-up (T4) (see **Figure 1**).

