##### Ayahuasca session procedure

2.7.2.1

Each ayahuasca session is conducted onsite over a 24-hour period, starting on Saturday morning. At 11:00 am, each participant is asked to attend an initial group meeting to discuss how the day will be organized. Immediately after that meeting, blood pressure and body weight are assessed by a medical doctor to ensure that this inclusion criterion is met, and to calculate the appropriate ayahuasca dose for each participant.

At 13:00h, a second meeting takes place to practice mindfulness exercises in a group format, which are aimed at promoting a low-avoidance and present-focused mindset during the psychedelic experience. Before the start of the first ayahuasca session at 14:30h, each participant takes part in a one-hour group dynamic during which they introduce their loved one to the rest of group, by sharing photos of the deceased (99). During the second ayahuasca session, this activity is replaced by an art-therapy activity, the dual rose technique, which can aid in the reconstruction of meaningful memories of the deceased and the relationship with them (107). Both activities help anchor the psychological content related to the loss in the participants’ mindset, immediately before the ayahuasca administration takes place.

During the ayahuasca session in the afternoon, participants recline on a comfortable couch in a quiet, ample room, while listening to the same instrumental music through a loudspeaker. They are encouraged to focus their attention inward, and research staff are always present in the room to address participants’ needs. Psychedelic effects typically last 5 hours, approximately, and participants are encouraged to describe their experience in writing during the 2 hours immediately afterward. Those who prefer to paint or draw to assimilate and express their experiences, instead of writing them down, are provided with the materials to do so.

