After this period of rest and reflection, a healthy vegetarian dinner is provided. Subsequently, participants sleep under medical supervision. The following morning, a light breakfast is served. Participants are then invited to optionally share their ayahuasca experiences in a group setting, expressing themselves as they feel comfortable. During this sharing, non-directive principles are followed to validate their psychedelic experiences. Before the session is over, they are provided with general information and advice regarding the sensitive state they may find themselves afterward, and how to manage it.

Ayahuasca sessions will be conducted in groups of up to eight participants, supported by a team of four facilitators. The primary responsibility of the facilitators is to ensure the physical and psychological safety and trust of participants throughout the session. They also provide non-directive support to help participants engage openly with their internal experiences as they emerge. The facilitator team includes the head of the Santo Daime Church (Barcelona), a psychiatrist (JJ), a nurse, and the principal investigator of the study (DG). All facilitators have extensive experience supporting individuals through altered states of consciousness. Their expertise spans religious settings, clinics treating treatment-resistant depression with ketamine-assisted psychotherapy, and several psychedelic research studies. They have also collaborated with retreat centers administering ayahuasca and psilocybin, in both traditional and non-traditional contexts.

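### Read literally, the rescue-medication sentence puts the first evaluation for drugs about 9–10 hours after ingestion, which conflicts with the emergency provisions that follow it

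*Protocol article*

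**What the plan says.** Section 2.7.2.2 of the Protocol article handles adverse effects in three consecutive subsections.

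- **Acute effects (2.7.2.2.1).** For marked distress, agitation, fear or paranoia, "facilitators will provide reassurance and encourage acceptance and curiosity toward the challenging internal experiences". Grounding techniques and a temporary move to a quiet space are also available. No drug is named.
- **Post-acute effects (2.7.2.2.2).** Effects are expected to last 5–6 hours, with up to 4 more hours of supervised rest. The measures are grounding, emotional regulation, herbal teas for nausea, and vital-sign monitoring of participants with adverse effects. No drug is named.
- **Rescue medication (2.7.2.2.3).** The opening sentence sets the time: "After monitoring post-acute effects for 4 hours, the medical team will evaluate the need for rescue medication if clinically indicated". The drugs follow: lorazepam for severe anxiety, olanzapine for agitation or psychosis, intramuscular clonazepam for extreme agitation with danger to the participant or others, a stepped regimen for pressure above 180/120 mmHg, metoclopramide for nausea and paracetamol for headache.

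Section 1.1 places distress in the acute phase: "some users have reported experiencing psychological distress during its acute effects".

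**The concern.** The opening sentence of the Rescue medication subsection gives a time, and no other sentence in the article gives a different one. Staff who work through the three subsections in order would use only non-drug measures through the whole acute phase and for 4 hours after it, and only then consider medication. Yet the conditions for which the strongest drugs are listed can arise while the brew is active; the Acute effects subsection itself lists agitation and paranoia.

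What is at stake is participant safety during dosing. Sample size, outcomes and analysis are untouched.

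**Working it through.** The article gives no figure for the interval from ingestion to rescue evaluation, so it has to be built from the parts.

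**Inputs**
- Duration of effects: 5–6 h (2.7.2.2.2); about 5 h in the session procedure (2.7.2.1).
- Post-acute monitoring before the drug evaluation: 4 h (2.7.2.2.3). This matches the up to 4 additional hours of rest in 2.7.2.2.2.
- Split dose: the second intake comes 30 minutes after the first (2.8).

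**Formula:** time to evaluation = duration of effects + post-acute monitoring.

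**Results, in hours after first intake**
- Main reading: 5 + 4 = 9 to 6 + 4 = 10.
- With the 5 h duration from 2.7.2.1: 5 + 4 = about 9.
- With the effects timed from the second intake: 0.5 + 5 + 4 = 9.5 to 0.5 + 6 + 4 = 10.5.
- With the 4 hours counted from ingestion, against the word post-acute: 4. Even then, 4 of the 5–6 hours of effects would pass before any drug evaluation, that is 4/6 = 67% to 4/5 = 80% of them.

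On the main reading, an emergency at the very end of the effects would wait 4 hours for evaluation, and an earlier one would wait longer.

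**Comparison with the rest of the subsection.** For severe hypertension, lorazepam may be given first, captopril 30 minutes later if pressure stays high, and a second captopril dose after another 30 minutes. If every step is used, amlodipine and emergency referral come after about 30 + 30 = 60 minutes. Olanzapine may be repeated after one hour. A regimen that escalates within an hour is hard to reconcile with a first evaluation 9–10 hours after ingestion.

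**Search for an exception.** No sentence in the article provides for an earlier drug evaluation, exempts emergencies from the wait, or gives a reason for it.

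**The case against.** The strongest reply is that the opening sentence only schedules a review of participants who still have symptoms after the rest period. The drug instructions that follow have their own severity triggers and do not repeat the wait. Staff are in the room throughout, the facilitator team includes a psychiatrist and a nurse, and its main duty is participants' safety. Competent clinicians would probably act at once.

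Much of this stands. A reader might infer that the protocol forbids rescue drugs during the acute phase, and the documents do not support that. But the drug instructions say which drug and how much, not when the need is assessed, and their silence does not cancel the one sentence that does give a time. A safety procedure should not depend on staff departing from its wording in an emergency.

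A second reply is that a journal article condenses the full protocol, so missing emergency detail is no fault. That is right as far as silence goes, but this point rests on a timing rule that the article states. It does rule out a related inference, that blood pressure goes unmeasured during the session. The article says that "blood pressure measurement is taken on-site before each ayahuasca session" and describes monitoring of affected participants afterwards. Its silence about the interval between proves nothing, and the Rescue medication subsection also calls for close monitoring in severe hypertension.

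A third reply is that the wait may be deliberate, because the brew inhibits monoamine oxidase and drugs could interact with it. The article does exclude people with potential pharmacological interactions, so the authors had the issue in mind. They do not give it as the reason for the wait, however, and a blanket wait would not be the clear way to express a drug-specific caution. The possibility is a good reason not to write an unrestricted permission.

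Finally, a reader might use the survey finding in section 1.1, that "2.3% reported requiring medical support following ayahuasca use", to forecast how many participants the wording would affect. It cannot carry that weight. It comes from a global survey of users, is not specific to rescue drugs or to the acute phase, and does not describe participants screened for hypertension and psychotic history.

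**Conclusion.** The point holds as a conflict within a safety procedure. Followed literally, the only stated timing rule places the evaluation for rescue drugs about 9–10 hours after ingestion, with only non-drug measures described before then. The same subsection provides for dangerous agitation and for pressure above 180/120 mmHg, with treatment steps measured in minutes.

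The 9–10 hours assume that the 5–6 hours of effects run from first intake and that post-acute monitoring begins when they end; timing from the second intake adds half an hour. An intended ban on earlier treatment is not shown, and the number of participants who might be affected cannot be estimated from the document. The correction is worth making because the wording bears directly on safety.

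**What to change.** Replace the first sentence of section 2.7.2.2.3 with:

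*The medical team will evaluate the need for rescue medication whenever clinically indicated from ingestion onward, without delay for severe agitation or psychosis with risk of harm or for blood pressure above 180/120 mmHg, taking account of interactions with ayahuasca; participants with residual symptoms after 4 hours of post-acute monitoring will be evaluated again.*

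If a wait is intended for a particular drug because of interactions, state it for that drug.

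The cost is one sentence of text, and the clinicians needed are already on the facilitator team. The real downside is that a drug might be given while the monoamine-oxidase-inhibiting brew is still active. The proposed wording leaves that decision to the medical team's judgement and requires interactions to be weighed.

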### Pharmacological analyses and dosification

2.8

A 10-liter batch of ayahuasca (i.e, *Daime* in Portuguese) will be donated by CEFLURIS (IDARIS), a Brazilian-based religious organization associated with the Santo Daime church. Following a ritual tradition, ayahuasca is prepared by boiling the stems of *B. caapi* (which are rich in harmine, tetrahydroharmine, and harmaline) together with the leaves of *P. viridis* (which are rich in N,N-dimethyltryptamine) for several hours. Analyses are conducted by Energy Control (energycontrol-international.org) using Liquid Chromatography-Mass Spectrometry (LC-MS). The ayahuasca will be stored in a refrigerator at -40°C to minimize degradation of DMT and alkaloids as much as possible (114).

A medium dose of ayahuasca (0.75 mg DMT/kg) will be orally consumed in two different intakes (0.30 mg DMT/kg as an initial dose and 0.45 mg DMT/kg after 30 minutes). With this method, it is expected that the monoamine-oxidase-inhibiting properties of the β-carbolines in the first dose will block the metabolic degradation of DMT by MAO-A, enabling full access to systemic circulation once the second dose is administered (115).

## Discussion

3

This clinical trial is the first to examine the potential of psychedelic-assisted grief therapy and, more specifically, of ayahuasca-assisted meaning reconstruction therapy for the reduction of the severity of grief symptoms. The study also investigates whether the intervention promotes quality of life and post-traumatic growth, while exploring a series of processes of change that may mediate this therapeutic effect. If this intervention proves to be both feasible and effective upon completion of this study, a future clinical trial will be designed with a focus on (a) prioritizing the mechanism(s) of change that will be identified through mediation analyses.

A key limitation of the trial is that the sequential allocation of participants may have a bias influence on the outcomes. Another limitation is a threat to external validity connected to the recruitment process: the self-referral process relies on the social media presence of psychedelic research and education institutions and associations, which may limit the generalizability of the clinical outcomes to the general population. Moreover, the fact that ayahuasca is a plant concoction complicates the determination of which alkaloids and active compounds influence the outcomes. Finally, accepting bereaved people who meet the ICD-11 sixth-month-since-the-loss criterion for PGD disorder (instead of the more conservative 12-month criterion) could blur the distinction between prevention and treatment. Nevertheless, we will also analyze PGD criteria following the ICD-11 as a potential moderator.

Given the lack of grief literacy in the general population, the widespread loneliness in Western society, and lack of mental health support during the early stages of bereavement, it is imperative to improve bereavement support for acute grief (13). The scarcity of evidence-based therapies for the prevention of PGD indicates the urgent need for new interventions to support bereaved people at moderate-to-high risk, according to the four-tier model (116). We anticipate that the outcomes of this trial will significantly contribute to the field of bereavement care, helping to reduce the time needed for the bereaved to receive evidence-based support, and promoting their adaptation. Moving beyond the context of grief and loss, this study will also contribute to advancing our understanding of PAP as way to prevent and reduce the global mental health burden (14).
